**Mental well-being**
Positive psychological well-being and depression symptoms
**Symptom distress**
Distress related to pain, heart, gastrointestinal, sexual dysfunction, and sleep and foot problems or symptoms
**Daily life with diabetes**
Fitting diabetes into daily life and diabetes-specific social support
**Worries due to diabetes**
Worry about disease progression, that is, diabetes complications
**Diabetes self-management confidence**
Confidence in managing diabetes (diet, physical activity, adjusting treatment, self-monitoring, and care seeking)
**Blood sugar regulation**
Perceived quality of blood sugar regulation and burden due to hypoglycemia and the fluctuation of blood sugar levels
**Medicine experience**
Efficacy, convenience, side effect distress, and satisfaction
**Access to care**
Confidence in ability to get in contact with a health care professional if needed in relation to diabetes
**Personal priorities for diabetes care**
Wish for support for specific aspects of self-managementPriority topics to discuss at the diabetes visit

The questionnaire consists of a combination of previously psychometrically validated items and scales, as well as newly adapted or designed items. Adaptation or design of new items was only done if no previously validated items were available that fit the requirements of people with diabetes and HCPs. In addition, a participatory and qualitative approach was used, including literature review, desk research, and qualitative research for each construct. It uses branch logic, so each person with diabetes only receives directly relevant questions. The psychometric validity, reliability of each item, and appropriateness of the scoring algorithms and logic rules will be examined in this study.

#### The Digital PRO Tool: DiaProfil

DiaProfil is a stand-alone PRO diabetes digital tool, codeveloped with the inputs of people with diabetes and HCPs by Aalborg University Hospital with the support of Zitelab, specifically for augmented use of the national PRO Diabetes Questionnaire as a tool for person-centered care delivery across care settings. An iterative, user-centered design process was undertaken involving people with diabetes and a multidisciplinary HCP team at Aalborg University Hospital to define optimal functionality and user interfaces. Previous experiences with other multidimensional PRO tools for diabetes were also considered [54].

DiaProfil allows the person with diabetes to complete the PRO questionnaire using mobile, tablet, or a PC and provides the HCP with web-based access to a multi-layered interactive PRO dashboard and an administrative system for reviewing and ordering PRO assessments. A significant new functionality in DiaProfil, resulting from the participatory design process, was the integration of actionable information for each PRO construct into the dashboard. The tool provided the HCP with information about available treatment and referral options, community services, and educational materials for each PRO construct. It required the clinical team to undertake an extensive desk-research exercise to map all resources and follow-up actions for each construct beyond its own care setting.

The DiaProfil dashboard was designed to provide an intuitive overview of the people with diabetes’ overall PRO results in one screen to allow HCPs to achieve an overview almost instantly, which can be useful in daily practice. Furthermore, the tool was developed for acceptability and readability for people with diabetes to facilitate collaborative use by people with diabetes and HCPs together on equal terms during the visit.

A screenshot of the DiaProfil PRO dashboard is shown in Multimedia Appendix 3.

The dashboard presenting the results is interactive and contains multiple layers of information that are accessible with one or two mouse clicks from the main screen. For each PRO topic and output, key information is obtained with a single click, including (1) dialogue tips and tools, (2) educational materials, (3) referral options, and (4) listing of locally relevant care and support options. For instance, if a person with diabetes likely had depression, the HCP could click on the topic on the screen to directly view information about local referral options and various psychosocial support and self-help resources.

DiaProfil was used in all participating study sites, except for one hospital that used the health platform tool.

#### The Danish Health Care Platform: Sundhedsplatformen

To integrate PRO data into their existing health information technology infrastructure, one hospital, Frederiksberg-Bispebjerg, used their existing generic IT health platform, EPIC, to collect and display PRO data. This platform is used by all hospitals covering 2.6 million inhabitants. In this hospital, people with diabetes completed the PRO Diabetes Questionnaire using the existing *My Health* app, which patients in the Capital Region of Denmark use to access general health care information. In this system, the HCP can view PRO results on multiple data screens that combine clinical and PRO data. Detailed methods for displaying PRO data on the clinical screen and ensuring proper placement in the patient flow were developed by the clinical diabetes care team together with the health information technology provider (Center for IT, Medico and Telephony) for optimal usability and integration into the existing workflow.

### Outcomes

#### Working Model for the Evaluation of the Process and Outcome Indicators

A conceptual model to illustrate the key hypothesized mechanisms of action, moderators, and outcomes for the PRO diabetes intervention is shown in Figure 2. This was used to guide the design of outcomes and data collection tools. The working model reflects preliminary data from the formative evaluation process of the PRO diabetes tool [1,11] and will be continuously updated and expanded with the progress of the study.

**Figure 2 figure2:**
[figure not shown]
A working model to illustrate hypothesized mechanisms, moderators, and impacts related to the use of the PRO diabetes tool. HCP: health care professional; PRO: patient-reported outcome.

The top part of the model illustrates that completion of PRO at home is hypothesized to impact care through mechanisms of reflection, motivation, and engagement before the visit and through mechanisms of active engagement of the people with diabetes and use of person-centered and value-based care strategies by the HCP during the visit. The use of PRO is hypothesized to lead to different follow-up actions by the health care team, which in turn is hypothesized to lead to different benefits for people with diabetes and HCPs. Both patient, health professional, and care setting factors are hypothesized to potentially moderate the extent to which use of the intervention impacts outcomes for people with diabetes and HCPs. Textbox 2 provides an overview of the main outcomes of this study.

Overview of the main outcomes of the study.
**Primary outcomes**
Perceptions of people with diabetes with regard to the following:Acceptability, usability, and appropriateness of the patient-reported outcome (PRO) intervention (outcome 1A)Impact (positive and negative) on them of using the PRO diabetes tool as part of their care (outcome 1B)Perceptions among health care professionals regarding:Usability, feasibility, fidelity and appropriateness of the PRO intervention (outcome 2A)Impacts (positive and negative) on diabetes care of using the PRO diabetes tool as part of routine care (outcome 2B)
**Secondary outcomes**
Psychometric and clinical validity and reliability of the PRO questionnaire, scoring algorithms, and clinical dialogue support (outcome 3)Barriers and facilitators for the implementation and impact of PRO diabetes tool for people with diabetes, for health care professionals, and at the health system level (outcome 4)Estimation of public health impact indicators of the PRO intervention according to the RE-AIM (Reach, Efficacy, Adoption, Implementation and Maintenance) model (outcome 5)

#### Primary Outcomes

This study uses two primary descriptive outcomes. First, data will be gathered on the perceptions of the usability, acceptability, and appropriateness of the PRO diabetes tool of people with diabetes, along with the perceived positive and negative effects of their use of the tool. Data extracted about their disease and care are classified by type of diabetes, age, gender, treatment modality, duration, disease complications, comorbidities, treatment setting, PRO outcomes, and general rating of visit quality (primary outcomes for people with diabetes). In addition, data will be collected on the HCP’s perception of acceptability, appropriateness, and perceived positive and negative effects of the tool on care quality and experience by HCPs. Furthermore, information on years of professional experience, years of diabetes experience, training in use of person-centered communication, confidence in use of PRO in visits, treatment setting, and general rating of visit quality (primary outcome for HCP) is also obtained.

Measures and data sources for outcomes pertaining to indicators of feasibility and implementation [55,56] are detailed in Multimedia Appendix 4.

#### Secondary Outcomes

Characterization of the validity and reliability of the PRO questionnaire and clinical algorithms is a secondary outcome of the study (outcome 3). This outcome is assessed in three ways. First, the people with diabetes’ perception of relevance, comprehensiveness, difficulty, acceptability, appropriateness, and comprehension of the questionnaire according to the type of diabetes, age, gender, treatment modality, duration of diabetes, disease complications, comorbidities, and treatment setting are measured (outcome 3A).

Next, the HCP’s evaluation of the clinical and face validity of the PRO data; the clinical relevance and utility of the PRO content, including the items, scoring, outputs, algorithms, and digital dialogue; and decision support are measured (outcome 3B).

Then, the psychometric properties of the questionnaire pertaining to the extent to which it provides valid, reliable measurements of the selected constructs, can predict relevant future clinical or care needs, events, and prognoses, and can discriminate appropriately between relevant levels of symptom severity are evaluated (outcome 3C).

We also assessed the barriers and facilitators at the people with diabetes, HCP, clinic, and health care system levels for the implementation and impact of the PRO diabetes tool as a secondary outcome (outcome 4). Finally, the initial indicators of the reach, efficacy, adoption, implementation, and maintenance of the intervention in accordance with the RE-AIM model will be examined (outcome 5). The measures and data sources used to evaluate the intervention according to RE-AIM indicators are detailed in Multimedia Appendix 5.

### Participant Timeline

All sites used the same core data collection and intervention procedure, as shown in Figures 3 and 4, with local modifications and adaptations, for seamless integration into routine care. Each participant was recruited approximately 14 days before their scheduled visit. People with diabetes will receive a link or electronic invitation to access and complete informed consent and the PRO Diabetes Questionnaire 2-14 days before their visit. People with diabetes will complete the PRO before their visit, unless there are specific barriers preventing this. At their scheduled visit, the HCPs use the IT PRO Dialogue Tool to review the results with the people with diabetes to support their dialogue. People with diabetes and HCPs will independently complete the evaluation forms when they are physically separated after the visit. Selected people with diabetes are invited for a 30- to 45-minute semistructured interview within 0-12 days after their diabetes visit. HCPs will participate in 4- to 5-hour multidisciplinary, structured HCP evaluation workshops halfway through and at the end of the study as well as complete individual end-of-study questionnaires.

**Figure 3 figure3:**
[figure not shown]
Timeline for people with diabetes participating in the study. PRO: patient-reported outcome.

**Figure 4 figure4:**
[figure not shown]
Timeline for HCPs participating in the study. HCP: health care professional; PRO: patient-reported outcome.

### Sample Size

As the study has descriptive purposes, formal requirements for sample size estimation for the primary outcome were not applied. However, for any subgroup analysis, the minimum number of patients per group was estimated to be 64. For continuous variables, a minimal subgroup size of 64 was estimated to achieve 80% power for detecting an effect size of 0.5 at a significance level of *P*=.05 by using a two-sided, 2-sample, equal-variance *t* test. For proportions, minimal group sample sizes were estimated to be 63 to achieve 80% power for detecting an effect size of 0.5 with a significance level of .05 by using a two-sided z test in a similar manner.

The minimum target for recruitment was 125 people with type 1 diabetes and 375 people with type 2 diabetes, based on requirements for comparatively analyzing by subgroups and requirements for psychometric analyses.

According to the available data, group comparisons will be undertaken using data across all centers by age groups, treatment modality (none, tablet only, short- and long-acting insulin, insulin pump, and glucagon-like peptide-1), blood sugar measurement technology (finger prick, flash glucose monitoring, and continuous glucose monitoring), diabetes complications (neuropathy, cardiovascular disease, gastrointestinal complications, sexual dysfunction, and sleep difficulty), and comorbidities.

Power analyses for comparative analyses will be conducted based on the final number of people with diabetes by site for PRO and PRO evaluation data to determine the extent to which outcomes can be comparatively analyzed either at the site or at the care-setting level.

The expected number of HCPs to participate was 25-40, based on what was reported to be feasible by the study sites. Sites were encouraged to have several HCPs participating as a minimum and to include HCPs with a good diversity of health care discipline, age, diabetes experience, and profession.

To compare experiences across different health care settings, the aim of this study was to include sites from secondary care, municipality rehabilitation centers, and primary care. On the basis of the resources available for the pilot study, the total number of sites was estimated to be 7-10.

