#### Data Collection for Secondary Outcomes: Predictors, Barriers, Facilitators, and Readiness Factors for the Adoption, Usage, Satisfaction, and Benefits of PRO

Sociodemographic and diabetes profile data were collected for all participating people with diabetes to analyze the known-group and discriminative validity and reliability of the PRO Diabetes Questionnaire together with primary study outcomes by people with diabetes subgroups. A core set of HCP profile data is collected for all HCPs to evaluate primary outcomes by the relevant HCP subgroups. Two comprehensive questionnaires are used—one adapted for use in Denmark for this study from the Primary Care Resources for Chronic Illness Care Questionnaire [57] (Multimedia Appendix 14) and one study-specific questionnaire. The study-specific questionnaire assesses details for each site about the local PRO setup and examines the extent to which the site has resources and services to follow-up on each PRO construct covered by the PRO Diabetes Questionnaire. These data are used to qualitatively analyze relationships between primary outcomes by contextual factors relevant to the delivery of person-centered and psychosocial diabetes care and the RE-AIM analysis.

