### Data Analysis

#### Statistical Methods

Quantitative data (ie, closed-ended questionnaire data and numerical data) will be coded, and all numerical data will be prepared for descriptive analyses and main statistical analyses using IBM SPSS Statistics for Windows (IBM Cooperation). The SAS statistical software package (SAS Institute Inc) is used for multilevel hierarchical regression analyses. Descriptive statistics will be used for continuous (mean and SD) and categorical (frequency and percentage) variables to analyze and compare evaluation data by center and subgroups. The aim of this study is to analyze drop-out data, including nonparticipation, attrition, and completion rates across centers, to characterize the generalizability of findings relating to population reach and outreach to vulnerable populations, and to compare implementation drivers across participating centers. Both parametric and nonparametric statistics were used for group comparisons based on the distribution of each data variable.

Missing value analysis, including the identification of variables missing completely at random or not at random, will be conducted for all variables.

PRO results are scored and analyzed as both raw and scored data using predefined clinical scoring algorithms according to subgroups of adequate sizes for multilevel regression and multilevel logistic regression models [59]. Multi-item scores will be transformed and standardized to a score range of 0-100.

For subgroup comparisons, two-tailed *t* tests and nonparametric statistics, such as the Mann-Whitney *U* test, are used. Multivariate mediation regression analysis will be used to examine the relative contribution of the different participant, treatment, and setting characteristics. Multilevel analyses will be used as feasible and required to separate the variance by people with diabetes, HCP, and care setting. Bonferroni and associated methods will be used to adjust P values for multiple comparisons. Intraclass coefficient analysis will be used to examine the level of agreement between HCPs and people with diabetes on the primary outcomes of the visits, which were evaluated both by people with diabetes and HCPs.

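### The 80% power at 64 per group is set for one unadjusted test at .05, but the plan adjusts subgroup P values for multiple comparisons, so at that minimum size the figure does not hold

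*Protocol article*

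**What the plan says.** The Sample Size section of the protocol article applies no formal sizing to the primary outcome, because the study is descriptive. It then makes a power claim for subgroups: "for any subgroup analysis, the minimum number of patients per group was estimated to be 64". The basis given for outcomes measured on a continuous scale is that "a minimal subgroup size of 64 was estimated to achieve 80% power for detecting an effect size of 0.5 at a significance level of" .05, and the calculation was done "by using a two-sided, 2-sample, equal-variance" t test. A parallel figure follows: "For proportions, minimal group sample sizes were estimated to be 63 to achieve 80% power for detecting an effect size of 0.5", with a two-sided z test at .05.

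The same section lists the factors for group comparison: age groups, treatment modality (five categories), glucose-measurement technology (three categories), five named complications, and comorbidities. It also promises power analyses on the final numbers, to decide whether outcomes can be compared by site or by care setting.

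The Statistical Methods section names two-tailed t tests and nonparametric tests for subgroup comparisons and adds that "Bonferroni and associated methods will be used to adjust P values for multiple comparisons". The article does not say which comparisons make up a family or how many there are.

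**The concern.** The sizing and the testing rule use different significance levels. The minimum of 64 is calculated at .05. The tests it is meant to support will be judged, after adjustment, at something nearer .05 divided by the number of comparisons. Both statements are fixed in the article, so this is not a detail left for a later analysis plan.

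At stake is how a subgroup result near the minimum size is read. The Study Objectives section says the work is to inform the design of future trials. If an adjusted comparison between groups of about 64 is not significant, a reader relying on the Sample Size section could take it as a fair test with 80% power. The true figure could be nearer one half.

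**Working it through.** **Inputs.** From the Sample Size section: n = 64 per group, standardised effect d = 0.5, two-sided α = .05, two-sample t test with equal variances. From its list of factors: three glucose-measurement categories give 3×2/2 = 3 pairs; five treatment modalities give 5×4/2 = 10 pairs. From the Statistical Methods section: Bonferroni-type adjustment, taken here as α/m for m comparisons. A family of m = 20 is an assumption. It can be reached on one outcome as 10 + 3 + 5 complications + 1 for age + 1 for comorbidity, but the article does not state it.

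**Step 1: reproduce the plan's figures.** Power is the upper tail of a noncentral t distribution with 2n − 2 = 126 degrees of freedom and noncentrality d√(n/2) = 0.5 × √32 = 2.828, beyond the two-sided critical value. At α = .05 this gives 80.1% for 64 per group and 79.5% for 63, so 64 is the smallest size that reaches 80%. For proportions, reading 0.5 as a standardised difference (arcsine scale), n = 2(1.960 + 0.842)²/0.5² = 62.8, which rounds up to 63. Both figures are right for one unadjusted test.

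**Step 2: put in the adjusted level.** Same formula, with α = .05/m:

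| Comparisons m | α = .05/m | Power at 64 per group, d = 0.5 | Detectable d at 64, 80% power | n per group for 80%, d = 0.5 |
|---|---|---|---|---|
| 1 | .0500 | 80.1% | 0.50 | 64 |
| 3 (glucose measurement, all pairs) | .0167 | 65.6% | 0.58 | 86 |
| 10 (treatment modality, all pairs) | .0050 | 49.1% | 0.66 | 109 |
| 20 (assumed family) | .0025 | 40.3% | 0.70 | 122 |

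A normal approximation, Φ(2.828 − z), agrees to within about two percentage points:
- m = 1: Φ(2.828 − 1.960) = 80.7%
- m = 3: Φ(2.828 − 2.394) = 66.8%
- m = 10: Φ(2.828 − 2.807) = 50.9%
- m = 20: Φ(2.828 − 3.023) = 42.3%

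For the z test with 63 per group, the figures at m = 3, 10 and 20 are 66.0%, 50.0% and 41.4%.

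**Step 3: how far this depends on group size.** The drop applies to groups at the minimum.
- The recruitment target is 125 + 375 = 500. Spread evenly over five modalities, that is 100 per group, and power at m = 10 is 75.6%.
- The 598 completers spread evenly would be about 119 per group, with 84.6% at m = 10. Even spreads are illustrative; the article does not give the split.
- At 125 per group, power is 93.8%, 86.7% and 81.4% for m = 3, 10 and 20.
- Type 1 against type 2 at the targets (125 v 375) keeps at least 96% up to m = 20.

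**The case against.** The strongest reply is that the article makes no error of arithmetic: it states its test, level and effect size, and 64 and 63 follow from them. The study is descriptive and formative, and the Data Monitoring section says that all primary analyses were single-arm and noncomparative, so no main conclusion depends on the 64. It is a minimum, and larger groups have more power. The wording on adjustment allows methods other than plain Bonferroni, and the choice of family is commonly left to an analysis plan.

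Much of this stands and limits the weight of the point. It does not remove the mismatch. The descriptive caveat covers the primary outcome; the same paragraph then makes a formal power claim for subgroups. The promised power check on final numbers is tied to site and care-setting comparisons, not to modality, technology, complications, age or comorbidity. A step-down method such as Holm still tests the smallest P value at .05/m, so it helps little when only one difference is real.

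Three stronger readings are tempting and are not supported.

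- **Subgroup power is 40–66% as a general fact.** That range needs groups at exactly 64, plain Bonferroni and families of 3 to 20. The lower end rests on a family the article does not define.
- **The type 1 target breaks the plan's own rule, since two groups of 64 need 128.** The article says "The minimum target for recruitment was 125 people with type 1 diabetes and 375 people with type 2 diabetes, based on requirements for comparatively" analysing subgroups and on psychometric needs. The listed comparisons use data across all centres, and the article nowhere specifies splitting the type 1 group in two. An even split of 125 would in any case give 79.2%.
- **Subgroups of health care professionals (HCPs) break the rule.** "The expected number of HCPs to participate was 25-40", and "A core set of HCP profile data is collected for all HCPs to evaluate primary outcomes by the relevant HCP subgroups". But the rule of 64 is worded for patients, the HCP number was set separately on feasibility, and the article promises neither tests nor 80% power for HCP subgroups.

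**Conclusion.** The point holds as a mismatch between the level used for sizing and the level used for testing. At the stated minimum of 64 per group, 80% power for an effect of 0.5 is true only of a single unadjusted comparison. Under strict Bonferroni it is about 66% for three comparisons and about 49% for ten. The ten assumes that every pair of treatment modalities is tested, which the article does not say. About 40% applies only if 20 comparisons are treated as one family.

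The weight is minor to moderate. The study is descriptive, its primary analyses do not depend on the figure, and groups well above 64 largely escape the problem. What needs correcting is the stated power of the subgroup comparisons.

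**What to change.** Restate the sample-size paragraph in one of two ways.

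1. Name the comparison family for each factor and give power, or the detectable effect, at the adjusted level. For example: with 64 per group and 80% power, the detectable effect is about 0.58 for the three pairs of a three-category factor and about 0.66 for all ten pairs of a five-category factor. Equivalently, 86 or 109 per group would be needed to keep an effect of 0.5 detectable.
2. Say plainly that the 80% refers to a single unadjusted exploratory comparison at the minimum group size, and that power is lower once P values are adjusted.

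The cost is a less favourable stated figure and a few sentences of text. No new patients are needed. The Study Status section says that recruitment was completed in January 2021, so the first option could use the actual group sizes.
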